# Effects of a clinical decision support system and patient portal for preventing medication-related falls in older fallers: Protocol of a cluster randomized controlled trial with embedded process and economic evaluations (AD*F*ICE_IT)

**DOI:** 10.1371/journal.pone.0289385

**Published:** 2023-09-26

## Abstract

**Background:**

Falls are the leading cause of injury-related mortality and hospitalization among adults aged ≥ 65 years. An important modifiable fall-risk factor is use of fall-risk increasing drugs (FRIDs). However, deprescribing is not always attempted or performed successfully. The AD*F*ICE_IT trial evaluates the combined use of a clinical decision support system (CDSS) and a patient portal for optimizing the deprescribing of FRIDs in older fallers. The intervention aims to optimize and enhance shared decision making (SDM) and consequently prevent injurious falls and reduce healthcare-related costs.

**Methods:**

A multicenter, cluster-randomized controlled trial with process evaluation will be conducted among hospitals in the Netherlands. We aim to include 856 individuals aged ≥ 65 years that visit the falls clinic due to a fall. The intervention comprises the combined use of a CDSS and a patient portal. The CDSS provides guideline-based advice with regard to deprescribing and an individual fall-risk estimation, as calculated by an embedded prediction model. The patient portal provides educational information and a summary of the patient’s consultation. Hospitals in the control arm will provide care-as-usual. Fall-calendars will be used for measuring the time to first injurious fall (primary outcome) and secondary fall outcomes during one year. Other measurements will be conducted at baseline, 3, 6, and 12 months and include quality of life, cost-effectiveness, feasibility, and shared decision-making measures. Data will be analyzed according to the intention-to-treat principle. Difference in time to injurious fall between the intervention and control group will be analyzed using multilevel Cox regression.

**Discussion:**

The findings of this study will add valuable insights about how digital health informatics tools that target physicians and older adults can optimize deprescribing and support SDM. We expect the CDSS and patient portal to aid in deprescribing of FRIDs, resulting in a reduction in falls and related injuries.

**Trial registration:**

ClinicalTrials.gov NCT05449470 (7-7-2022).

## Background

Falling among adults aged 65 years and older represents a serious public health problem. Approximately 30% of adults aged 65 or older falls each year. Moreover, falls are the leading cause of injury-related mortality and hospitalization, with one out of five falls resulting in severe injury [1]. In the Western European region, 8.4 million adults aged 70 and older sought medical attention due to a fall-related injury, and 54 504 older adults died due to falls in 2017 alone [2]. The incidence rate of fall-related injuries increases substantially with age [2].

Besides physical injuries such as head wounds and fractures [3, 4], falls can also lead to the development of fear of falling [5, 6], reduced perceived quality of life [7], reduced physical activity [8], physical decline [9], social isolation [10], increased healthcare utilization, and institutionalization [9, 11, 12]. Furthermore, falls pose a substantial economic burden as fall-related costs are estimated to amount to 0.85 to 1.5 percent of the total healthcare expenditures in Western countries [13].

Falls have a complex etiology and are associated with several risk factors, such as history of falls [14], impaired mobility [14], frailty [15], chronic health conditions [16], fear of falling [17], depression [18], cognitive impairment [19], increasing age [18], and female gender [18]. In addition, a large body of research has linked the use of certain medications to falls [20–22]. Medications recognized as fall-risk increasing drugs (FRIDs) include antipsychotics, antidepressants, diuretics, and opioids [23]. Studies have reported that 65 to 93 percent of older adults admitted with fall-related injuries use at least one FRID [24]. Antidepressants were the most commonly used FRID at the time of the fall-related injury, with a prevalence between 15 and 40 percent [24].

Despite the growing evidence on medication as an important modifiable risk factor, deprescribing in older adults is often not attempted or performed unsuccessfully. Physicians generally find deprescribing challenging since it requires complex decision-making in the context of polypharmacy and multi-morbidity [25]. To be precise, physicians find it difficult to identify which patients are at risk of a medication-related fall and it is not always clear which medications should be considered for withdrawal and whether safer alternatives are available. Moreover, patients’ beliefs regarding their medication use may further hinder effective FRIDs deprescribing. Research indicates patients are generally not concerned about possible adverse effects from their regular medication and not aware of medication management as an effective fall-prevention strategy [26, 27]. More effective communication may help raise awareness and consequently prompt patients to adopt to and comply with deprescribing as a treatment option. Moreover, communication is a two-way process and research suggests that interventions targeting both physicians and patients may be more effective than interventions that only target either one [28]. Given these multifaceted complications, a multicomponent intervention is expected to improve FRIDs deprescribing in older adults and thereby help prevent medication-related falls.

There is growing attention for the role of SDM in deprescribing [29–31]. SDM can be defined as an approach where clinicians and patients share the best available evidence when making decisions. In doing so, patients are supported to consider options and to achieve informed preferences [32]. In complex patient cases with multiple treatment options, as is often the case in deprescribing in older adults, SDM has been found to lead to more informed decision-making, better participation in decision-making, more self-efficacy, increased knowledge, and reduced decisional conflict of patients in disadvantaged groups, such as older patients [33–35]. Therefore, it is expected that enhanced SDM would support the FRIDs deprescribing process as well as improve patient compliance and adherence to the new treatment plan. This, in turn, may lead to a decrease in medication-related falls among older adults.

Clinical decision support systems (CDSS) may help physicians in the deprescribing process of FRIDs and may stimulate SDM. A CDSS is a computerized system that aims to support clinical-decision making by generating assessments or recommendations based on the characteristics of an individual patient. CDSSs generate patient-specific output based on an existing knowledge base or based on predictive modelling methods. CDSSs are increasingly used for improving adherence to clinical guidelines as well as for preventing prescription errors and checking for drug interactions [36]. Use of CDSSs in the prevention of falls has been studied in in- and outpatient settings [37–40]. However, these studies were all limited in scope as they focused on a select number of FRIDs, did not use utilize predictive modelling methods for generating patient-specific output, or did not address risk communication or shared decision-making (SDM) [37–40].

A tool that could stimulate patients to participate in SDM is a patient portal, which allows patients to access their clinical data through a secure website [41]. A recent systematic literature review on the impact of patient portals on health outcomes found that patient portals can enhance preventive behaviors and adherence to therapy [42]. Furthermore, a qualitative study revealed that patients thought that a portal would facilitate them in seeking medical advice in between visits (e.g., on medication side effects) and that this would stimulate patient-driven communication [43].

Given this backdrop, the AD*F*ICE_IT project (Alerting on adverse Drug reactions: Falls prevention Improvement through developing a Computerized clinical support system: Effectiveness of Individualized medicaTion withdrawal) was initiated to develop and evaluate a multicomponent intervention for optimizing FRIDs deprescribing and consequently improve patient outcomes. The intervention comprises the combined use of a CDSS and a patient portal. The CDSS includes a personalized fall risk prediction, which is used to estimate and visualizes a patient’s fall risk. Furthermore, the CDSS gives insight in which of the patient’s medications can contribute to this fall-risk, provides suggestions with safer medication alternatives, provides guideline-based medication advice, and provides an overview of the possible treatment actions. The patient portal provides general fall-related educational information (e.g. information about falls prevention, FRIDs, and FRIDs deprescribing) and information to help patients prepare for their visit to the falls clinic. After the falls clinic visit, the patient portal will show a summary of the patient’s treatment plan as discussed during the consultation. These features of the CDSS and patient portal may help to optimize and enhance (shared) decision making during the consultation. Consequently, it is expected that this will lead to less injurious falls among older adults and reduce healthcare-related costs.

The primary aim of the AD*F*ICE_IT cluster randomized controlled trial is to assess the effectiveness of the multicomponent intervention, comprised of a CDSS and patient portal, compared with usual care. Effectiveness will be assessed in terms of time to first injurious fall (primary outcome). In addition, as secondary aims we will study the cost-effectiveness and feasibility of the intervention.

## Methods

The SPIRIT criteria were used as guideline for the reporting of this protocol paper [44] (S1 File). The *CONSORT 2010 Statement*: *extension to cluster randomised controlled trials* will be used to further guide the reporting of the results of the trial [45].

The design and the development of the AD*F*ICE_IT intervention was guided by the Medical Research Council (MRC) Framework for Complex Interventions [46]. In the preparation phase of the MRC framework, we developed a prediction model for estimating a patient’s risk of falling [47]. The prediction model is currently being externally validated. In the development phase, we identified evidence and theory regarding CDSS and patient portal end users’ preferences and needs, and extended these with empirical research (i.e. survey [48]), interviews) to inform our decisions regarding the design of the intervention. Furthermore, we incorporated guideline- and expert consensus-based medication advices (e.g. deprescribing advice or use of safer alternative medication) in the CDSS [23]. In the feasibility/piloting phase of the MRC framework, we tested the usability of the user interface of our intervention through usability studies. The present paper describes the protocol for the final phase of the project in which we will evaluate the effectiveness of the intervention.

### Study design and settings

To evaluate the effectiveness of our multicomponent (CDSS and patient portal) intervention in preventing injurious falls among older adults, a multicenter cluster-randomized controlled trial will be conducted among new falls clinic patients of ten Dutch hospitals. These patients have been referred for a multifactorial falls assessment to the geriatrics departments by their general practitioner, the emergency department, or other specialists because of a history of falling or an increased risk of falling.

### Ethical considerations

The ADFICE_IT study protocol was reviewed and approved by the Medical Ethics review board of the Amsterdam University Medical Centres (METC AMC 2021_061). All study participants will asked to sign an informed consent prior to data collection. The trial is registered with ClinicalTrials.gov (DATE; 7-7-2022, identifier: NCT05449470).

### Eligibility criteria

The study population consists of older adults visiting a falls clinic. Falls clinics typically perform detailed multidisciplinary fall risk assessments and make recommendations or implement a range of targeted falls and falls injury-prevention strategies based on the assessment findings [49]. Falls clinics at Dutch hospitals that use Epic software (Epic Systems Corporation; Verona, Wisconsin, United States) as their electronic patient record system were eligible to be included as a study center. Patients meeting the following criteria are eligible for inclusion:

Aged 65 years and older;History of at least one fall in the past year;A Mini-Mental State Examination (MMSE) score of 21 points or higher or equivalently a Montreal Cognitive Assessment (MOCA) Dutch score of 16 points or higher [50];Use of at least one FRID (as defined by the Dutch Federation of Medical Specialists [51]);

Sufficient command of the Dutch language in speech and writing; andWillingness to sign informed consent.

Potential subjects will be excluded if they:

Already participate in another (intervention) study;Have a life expectancy of less than one year; orSuffer from severe mobility impairment (i.e. bedridden, e.g. inability to walk short distances with assistance of a walking aid).

Participant recruitment has started in July 2022 and is ongoing.

### Randomization and blinding

Since the intervention needs to be integrated into the physician’s workflow, randomization will be performed at hospital level prior to the start of inclusion. We evaluated use of the CDSS in usability studies among physicians of one of the locations of the Amsterdam UMC, i.e. location AMC. To avoid possible contamination of the intervention, the Amsterdam UMC: location AMC will be exempted from randomization and included in the intervention group by default. To assure the control and intervention hospitals remain similar with respect to their patient population, the other location of Amsterdam UMC, i.e. location VUmc, will be included in the control group by default. Randomization of the remaining hospitals will be done based on a 1:1 allocation ratio and stratified based on whether the hospital is academic or non-academic. The randomization procedure will be done by an independent statistician using computer-generated random numbers. Blinding of the intervention allocation is not possible since both physicians and patients will have to interact with the CDSS and patient portal. Researchers will be blinded to group allocation during the statistical analyses.

### Intervention

The multicomponent intervention comprises the combined use of a CDSS and a patient portal. Furthermore, patients in the intervention arm will receive a Question Prompt List (QPL) prior to their consultation. Physicians in the intervention arm will be trained to work with the CDSS. The control hospitals will only receive a general overview of the study, including the procedures. Patients in the control arm will receive care-as-usual.

#### CDSS

Relevant FRIDs were identified based on the Dutch fall guideline [51] and STOPPFall (Screening Tool of Older Persons Prescriptions in older adults with high fall risk) tool [23]. These two sources form the foundation for the CDSS’ clinical knowledge base. For each class of identified FRIDs, relevant recommendations about deprescribing from more than 30 different Dutch clinical guidelines have been extracted and formalized using the Logical Elements Rule Method [52]. Thus, the CDSS provides point-of-care guideline and expert consensus based medication withdrawal advice [23] as well as a personalized fall-risk estimation based on a prediction model [47].

The CDSS will be integrated in the electronic patient record system and workflow of physicians. On the CDSS start page, the physician can check the data that was pulled from the electronic patient record system, and see the patient’s estimated risk of falling. On the next screen, the physician can see the advice of the CDSS for each of the patient’s prescribed current medications. Based on the given advice, the physician can decide to propose a change in treatment for a specific medication. The physician can discuss those proposed treatment changes with the patient using the consultation screen. The final screen will allow the physician to copy-paste all treatment decisions to the patient’s electronic health record, print a patient-friendly summary of the individual treatment plan, and send it to the patient portal.

#### Patient portal

Patients in the intervention arm will receive access to the patient portal prior to their visit to the falls clinic. At that time, the patient portal provides general fall-related educational information (e.g. information about falls prevention, FRIDs, and FRIDs deprescribing) and information to help patients prepare for the falls clinic visit. After their consultation with the physician during their fall clinic visit, the patients will also receive access to the additional patient portal pages with the personalized fall-risk estimate and the treatment plan as discussed with the physician.

#### Question Prompt List (QPL)

Patients in the intervention arm will receive a printed QPL prior to their visit to the falls clinic. A QPL is a structured list of questions designed to encourage information gathering, which patients can use as example questions to ask during the consultation [53]. A QPL stimulates agenda setting and helps patients to remember important questions. In other contexts (e.g. oncology), QPLs have been found to improve communication and stimulate participation in older patients [53]. Our QPL will consist of preparatory questions and concerns that need to be completed by the patient preceding the consultation (e.g. ‘Which of the medications that I am currently taking are truly crucial for my health?’). Patients will be asked to bring it with them to consultation.

#### Training

Physicians will be trained in small groups (i.e., the geriatric staff of a specific intervention hospital) on how to use the system during a one-hour training session. The training addresses four components: 1) general overview of the study and its aim, 2) (issues in) FRIDs deprescribing, 3) employing SDM and the QPL during a consultation, and 4) practical instructions on how to use the CDSS. AD*F*ICE_IT project team members (i.e., an experienced geriatrician and two communication scholars) will provide the training. Afterwards, an online version of the training will be available to the physicians.

### Comparator

Patients treated at the control hospitals will receive care-as-usual, e.g. a multifactorial fall assessment at a falls clinic. Usually such an assessment takes up around 3–4 hours, distributed over 1 or 2 days, and is concluded by a consultation between the patient and the physician.

### Procedures

Patients who schedule an appointment at any of the participating falls clinics (i.e., intervention and control hospitals) will receive a letter containing information on the objectives and procedures of the study and an invitation to participate. For patients in the intervention arm, the invitation letter will also include a printed QPL and a link to the patient portal.

At the falls clinic, eligibility will be determined according to the in- and exclusion criteria by the hospitals’ staff members. The researcher will then provide oral and written information about the study to eligible patients. Patients who are interested in participating in the study will be asked to sign an informed consent form. Next, the falls clinic assessments will be carried out as usual. In the intervention group, the physician will use the CDSS prior to the consultation to understand a patient’s fall risk and medical background as well as during the consultation with the patient. Consultations in the control group are carried out according to care as usual. After the consultation, the research assistants will ask the included patients and their caregivers (if applicable) to fill out a set of questionnaires (see “Data Collection”). After the visit to the falls clinic, patients in the intervention group will be able to review information about their consultation with the physician (i.e., their treatment plan) and their estimated fall risk in the patient portal.

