### Data collection

We will collect a wide range of quantitative and qualitative data to assess the effectiveness and cost-effectiveness and to evaluate the implementation of the intervention (see Fig 1 for complete overview of measurements). Questionnaires will be administered at baseline and 3, 6, and 12 months after baseline (Fig 1).

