### Estimating the effectiveness of the intervention on trial outcomes

The primary outcome is time to first injurious fall. An injurious fall is defined as a fall resulting in wounds, bruises, sprains, cuts, medically recorded fractures, head or internal injury, requiring medical/health professional examination, accident and emergency treatment, or inpatient treatment [54]. This definition is consistent with moderate and serious injuries, as proposed by Schwenk (2012). Secondary outcomes include number of injurious falls, total number of falls, time to first fall resulting in any injuries (i.e., fall that results in minor, moderate, or severe injuries), total number of falls resulting in any injuries, time to first fall and (health-related) quality of life. Falls are defined as an unexpected event in which the participants come to rest on the ground, floor, or lower level [55]. At baseline, patients in both groups receive a falls calendar to keep track of falls, fall-related injuries, and fall-related healthcare use on a weekly basis for 12 months. The falls calendars will be returned every month by mail. Incomplete, missing or unclear data will be further inquired by telephone. Health-related) quality of life is assessed using the EuroQol-5D-5L (EQ-5D-5L) index value, EQ-5D visual analogue scale and the Older Persons and Informal Caregivers Survey Short Form (TOPICS-SF) summary score [56, 57]. EQ-5D-5L is a standardized instrument for measuring health-related quality of life [58]. The health states based on the five EQ-5D-5L domains will be converted to utility scores using the Dutch EQ-5D-5L tariff [56]. The TOPICS-SF is a 22-item questionnaire for measuring health-related quality of life, which was developed to evaluate patient-reported outcomes in the context of multidimensional geriatric care [57].

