### Estimating the effectiveness of the intervention on trial outcomes

For every participant, we will assess fall incidents during a fixed follow-up period of 12 months, which will start after a set 1 month, during which the dose of FRIDs will be stopped or decreased. Difference in time to injurious fall between the intervention and control group in the follow-up period will be analyzed by means of a multilevel Cox regression model based on hospital level [69]. Model fit will be assessed using standard approaches (e.g., the proportional hazards assumption with Schoenfeld residuals). We will adjust all models for age, sex and type of hospital, i.e. academic versus non-academic. In a sensitivity analysis, we will additionally adjust for significant baseline differences. Difference in total number of (injurious) falls in the follow-up period between the control and intervention groups will be analyzed by means of multilevel Poisson regression models based on hospital level. In the case of overdispersion, we will apply either quasi-Poisson regression or negative binomial regression depending on the observed distribution of the data. Difference between the intervention and control group with respect to time to any fall and time to fall that results in any injuries will be analyzed by means of survival analyses, similarly to the primary outcome.

Differences in EQ-5D-5L index score, EQ-5D visual analogue scale, and TOPICS-SF summary score between the intervention and control group after 12 months will be analyzed by means of linear mixed models. These models will be adjusted for the baseline value of the outcome [70].

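### The quality-of-life baseline appears to be measured after the intervention consultation, yet the 12-month models adjust for it

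*Protocol article*

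**What the plan says.** The Procedures section of the protocol article sets out the visit in order: eligibility, consent, the usual falls-clinic assessments, the consultation, and then questionnaires. On the last step it says: "After the consultation, the research assistants will ask the included patients and their caregivers (if applicable) to fill out a set of questionnaires". It refers the reader to Data collection, which gives the occasions only as follows: "Questionnaires will be administered at baseline and 3, 6, and 12 months after baseline". That section leaves the full overview to Fig 1, which is not reproduced in the text at hand.

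Two parts of the intervention come before the questionnaires. One arrives by post: "For patients in the intervention arm, the invitation letter will also include a printed QPL and a link to the patient portal". The other is the consultation itself: "In the intervention group, the physician will use the CDSS prior to the consultation to understand a patient’s fall risk and medical background", and the system is used during the consultation as well.

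On outcomes, the article says that "quality of life is assessed using the EuroQol-5D-5L (EQ-5D-5L) index value, EQ-5D visual analogue scale" and the TOPICS-SF summary score. Under Statistical analysis, differences in these scores "between the intervention and control group after 12 months will be analyzed by means of linear mixed models", and: "These models will be adjusted for the baseline value of the outcome".

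**The concern.** Adjusting for a baseline score is sound when the score is taken before the arms are treated differently. Any baseline difference between arms is then chance or cluster imbalance, and adjustment removes it. If the score is taken after part of the intervention has been delivered, a baseline difference may itself be an effect of the intervention, and the model corrects for it as though it were imbalance.

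The three measures here are self-ratings. A consultation that presents a fall-risk estimate and questions current medication could change how a patient rates their health that day. At stake is the 12-month quality-of-life comparison on three secondary outcomes, and the QALY estimate if it uses the same baseline utility.

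**Working it through.** The plan gives no figure for this point. Its sample size concerns the primary outcome and does not bear on it. The check is therefore a reading of the sequence, followed by the algebra of the adjustment.

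**1. Sequence, from Procedures, Data collection and the Intervention section**

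| Step | Intervention arm | Control arm |
|---|---|---|
| Invitation letter | study information, question prompt list, portal link | study information |
| Consent, usual assessments | same | same |
| Consultation | decision support system used before and during it | care as usual |
| Questionnaire set | after the consultation | after the consultation |
| After the visit | personal risk estimate and treatment plan in the portal | none |

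No other questionnaire occasion at the visit is described, and nothing in the text places the quality-of-life forms earlier. On the plain reading, the set in the fourth row is the baseline measurement.

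**2. Effect of the adjustment**

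Let D12 be the true between-arm effect at 12 months, d the between-arm shift already present in the baseline score, and b the within-arm slope of the 12-month score on the baseline score. Then

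adjusted estimate = D12 − b × d.

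With a baseline taken before any intervention, the expected d is 0 and the estimate is D12.

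**3. Numbers (b and d are assumptions; the documents give neither)**

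On the visual analogue scale, with b from 0.5 to 0.7:
- d = 0: change 0.
- d = 2 points: 0.5 × 2 = 1.0 to 0.7 × 2 = 1.4 points taken off the estimate.
- d = −2 points: the same amounts added to the estimate.

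As a share of the 12-month effect, with f = d / D12, the part retained is 1 − b × f:

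| b | f = 0 | f = 0.10 | f = 0.25 | f = 0.50 |
|---|---|---|---|---|
| 0.4 | 1.00 | 0.96 | 0.90 | 0.80 |
| 0.6 | 1.00 | 0.94 | 0.85 | 0.70 |
| 0.8 | 1.00 | 0.92 | 0.80 | 0.60 |

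A shift opposite in sign to the 12-month effect makes f negative and inflates the estimate. For example, f = −0.25 with b = 0.6 gives 1 + 0.15 = 1.15.

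**4. Simulation check**

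The check used 1,000 data sets per setting, each with ten clusters of 77, an intraclass correlation of about 0.01, an assumed 12-month effect of 0.30 SD and b = 0.6. The model was a linear regression on arm and baseline score.

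| f | Formula: 0.30 × (1 − 0.6f) | Simulated, adjusted | Simulated, unadjusted |
|---|---|---|---|
| 0 | 0.30 | 0.30 | 0.30 |
| 0.25 | 0.255 | 0.25 | 0.30 |
| 0.50 | 0.21 | 0.21 | 0.30 |
| 1 | 0.12 | 0.11 | 0.29 |

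The formula holds up to simulation error, and the unadjusted difference does not depend on f.

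**The case against.** The strongest reply is that the timing is inferred. The Procedures sentence speaks of a set of questionnaires, does not call it the baseline set and does not list its contents. Several instruments ask about the consultation and have to follow it: the patient and physician measures of shared decision making, decisional conflict and, in the subsample, recall. Those alone would explain the sentence, and Fig 1 may place the quality-of-life forms earlier. This stands as a limit on certainty. It does not remove the point, because the text describes no earlier occasion.

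The second reply is that d may be nil. Control patients also finish a multifactorial assessment with a physician consultation, so only the added effect of the decision support system, prompt list and general portal pages counts. Medication reduction, the main route to benefit, is given a set month under Statistical analysis and cannot have acted on the day. The personal portal pages open only after the consultation. All of this stands, and it is why d is probably small.

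The third reply concerns the remedy. The prompt list and portal link arrive with the invitation, so a form completed after consent still follows some exposure. Reordering the forms during recruitment also produces two kinds of baseline. Both are true and belong with the costs.

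A reader might infer that the quality-of-life result is biased, or that part of the benefit will be adjusted away. The documents do not support this. They give no evidence of a same-day difference between arms, and a shift in the opposite direction would enlarge the estimate.

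**Conclusion.** The point holds as a conditional one. On the plain reading of the text, the covariate in the 12-month quality-of-life models is measured after most of the intervention contact at the visit. The estimate then moves by b × d. That is zero if the consultation causes no differential shift, and 1.0 to 1.4 visual analogue scale points under the assumed d of 2 and b of 0.5 to 0.7. The sign is not known in advance. The conclusion assumes that Fig 1 does not place these instruments before the consultation.

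The scope is limited to the EQ-5D-5L index, the EQ visual analogue scale and TOPICS-SF. QALYs are affected only if they use the same baseline utility, which the cost-effectiveness section does not say. The primary Cox model adjusts for age, sex and hospital type and is untouched. Its sensitivity analysis, which adds significant baseline differences, would be touched only if questionnaire scores were among them.

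**What to change.** 1. If Fig 1 or the full protocol already places the quality-of-life forms before the consultation, say so in one sentence under Procedures. Nothing more is then needed.
2. Otherwise, administer EQ-5D-5L (with its visual analogue scale) and TOPICS-SF after consent and before the physician consultation. The article describes an assessment of about 3–4 hours over 1 or 2 days that ends with that consultation, so there is room for them. Keep the shared-decision-making questionnaires about the consultation after it.
3. For patients already enrolled, keep the planned baseline-adjusted model and add a sensitivity analysis that omits the post-consultation baseline value but still adjusts for age, sex and hospital type. Record for each patient which timing applied.

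**Cost.** The change is to the order of forms plus a procedure note, and total questionnaire time is the same. Recruitment was ongoing when the article was written, so baseline timing would be mixed across the recruitment period. The sensitivity analysis is less precise and less protected against imbalance. That matters with ten hospitals, two of them allocated by default. Exposure to the mailed prompt list and portal link remains, so the change reduces the possible bias without removing it.
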